#### Assessing Trunk Stiffness Using Unpredictable Multi-directional Loads (Standing):

The same paradigm described above will be repeated with the healthy participant in a standing posture. This will allow us to examine the effects of posture (i.e., sitting versus standing) and sex (male, female) on trunk stiffness in a healthy cohort.

### Assessing Trunk Displacement Using Internally Generated Trunk Perturbations

To assess the effects of sex on trunk displacement with internally generated perturbations, participants will be asked to perform the following 3 rapid (duration of 100 ms) voluntary movements while in a standing posture: 1) flex both shoulders 90° to create a trunk flexion perturbation, 2) abduct the left shoulder 90° to create a trunk side-bending left perturbation, and 3) flex the right shoulder 90° while simultaneously extending the left shoulder 90° to generate a trunk rotation left perturbation. The participants will 6 trials of each of these tasks performed in a random order. To normalize the magnitude of the internally generated force, participants will perform the rapid shoulder movements with weights equal to 5% of body mass. Thus a participant weighing 120 lbs will hold a total of 6 lbs of weight to compete the task. The primary dependent measure is trunk displacement in the three-cardinal planes.

## NUMBER OF SUBJECTS AND POWER

The primary dependent variable (DV) for the **Experiment 2** group in the RELIEF study is the short-latency stretch reflex amplitude. Our preliminary work indicates that spinal manipulation reduces stretch reflex amplitude in individuals with chronic LBP who exhibit an audible joint sound by 30% from 0.56 to 0.39.[61] In study participants with no audible joint sound, there was a non-significant 10% increase from 0.62 to 0.68. The baseline standard deviation was 0.25 for both groups. We assumed manipulation would result in a 25% reduction 2-days following a course of treatment and a 20% reduction 4-weeks post course of treatment. Given our pilot data indicating the importance of cavitation, we assumed smaller reductions in stretch reflex amplitudes at each time point for the joint mobilization treatment arm. (i.e., 28, 23, and 18% reductions at the three endpoints). Finally, we assumed that Sham Control would have the same mean (0.68) at each testing point. Based on these data, in order to achieve adequate power, Experiment 2 required a total of 60 participants with chronic LBP that met a modified clinical prediction rule for spinal manipulation. Due to the greater prevalence of LBP in women, our sample for Experiment 2 will consist of 33 females and 27 males.

To address aim 1, we will recruit 60 healthy participants with no history of LBP matched on gender, age ( $\pm 3$  years), height ( $\pm 2$  inches), and weight ( $\pm 10$  lbs) to the LBP group. A recent paper by Vazirian et al reported large effects sizes ( $\eta^2=0.425$ ) for sex differences in sagittal plane trunk stiffness in healthy participants.[65] Based on these data our sample of 120 participants (60 participants LBP, 60 matched controls) will provide power of 0.85 to determine an interaction of sex by back pain group for trunk stiffness at  $p<0.05$ .

Given that our initial power estimates for the parent R01 (i.e., RELIEF study) were designed to detect gender differences as well as treatment effects on trunk onset muscle latencies, and assuming similar effect sizes for our trunk stiffness measures, 60 participants with chronic LBP should provide sufficient power for the stiffness measures in aim 2 of this application.

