## Exclusion criteria

Participants must not have any of the following exclusion criteria to participate in this study:

- Have a personal history of the following neurological disorders: Alzheimer's, Amyotrophic Lateral Sclerosis, Multiple Sclerosis, Parkinson's, or Stroke.
- Have a personal history of the following cardiorespiratory disorders: Congestive heart failure, Heart attack in past 24 months.
- Have a personal history of the following musculoskeletal disorders: Rheumatoid Arthritis, pathologic fractures of the spine, avascular necrosis or osteonecrosis, severe osteoarthritis. Including a history of spine surgery or a hip arthroplasty.
- Have active cancer.
- Be Blind.
- Have used narcotics or muscle relaxants within 30 days prior to study enrollment.
- Report being pregnant.
- Have a body mass index greater than 35 kg/m^2.
- Have clinical depression (i.e., subjects who score 24 or higher on the Center for Epidemiology Depression Scale).
- Current drug or alcohol use or dependence that, in the opinion of the PIs, would interfere with adherence to study requirements

## Hypothesis Testing: Aim 1

Hypothesis 1.1. Male participants with chronic LBP will present with increased stiffness compared female participants with chronic LBP

Hypothesis 1.2. Participants with chronic LBP will present with increased stiffness compared healthy controls.

Separate 2 Group (Chronic LBP, Matched Healthy Control) x 2 Sex (Male, Female) mixed-model MANOVAs will be conducted on trunk stiffness measures.

## Hypothesis Testing: Aim 2

Hypothesis 2.1. There are no net sex effects of spinal manipulation on trunk stiffness.

Hypothesis 2.2. Both manipulative interventions will decrease passive trunk stiffness as evidenced by the trunk's initial mechanical response to multi-directional trunk perturbations.

Separate 3 Group (Manipulation, Mobilization, Sham Laser) x 2 Gender (Male, Female) x 3 Time (Baseline, Immediately following initial treatment, 48 hrs post-3 weeks of treatment) mixed-model MANOVAs will be conducted on trunk stiffness measures.

**Specific Aim 3.** To examine the effects of sex and posture on trunk stiffness.

**Hypothesis 3.1.** Healthy Male participants will present with increased trunk stiffness compared to healthy female participants.

**Hypothesis 3.2.** Trunk stiffness will be greater in sitting compared to standing.

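### Aim 1 of the supplement: the stated 0.85 power for a sex-by-back-pain interaction does not follow from the effect size cited, and neither Aim 1 hypothesis is an interaction

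*Supplement*

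**What the plan says.** The power paragraph for Aim 1 is in the Appendix (Supplemental), under Number of Subjects and Power. It cites one earlier study, which "reported large effects sizes ( $\eta^2=0.425$ ) for sex differences", and specifies that the result is "for sex differences in sagittal plane trunk stiffness in healthy participants". The sample is described as "our sample of 120 participants (60 participants LBP, 60 matched controls". The claim drawn from the cited study, at a significance level of 0.05, is that this sample "will provide power of 0.85 to determine an interaction of sex by back pain group for trunk stiffness". The same section fixes the sex split: "our sample for Experiment 2 will consist of 33 females and 27 males". Controls are matched on sex, so they have the same split.

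The section Hypothesis Testing: Aim 1 lists two hypotheses. H1.1 is "Male participants with chronic LBP will present with increased stiffness compared female participants with chronic LBP". H1.2 is "Participants with chronic LBP will present with increased stiffness compared healthy controls". The planned analysis is "Separate 2 Group (Chronic LBP, Matched Healthy Control) x 2 Sex (Male, Female) mixed-model MANOVAs will be conducted on trunk stiffness measures". The appendix gives no interaction effect size, standard deviation, cell means or power formula for Aim 1, and no power for H1.1 or H1.2.

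**The concern.** There are three faults in the one sentence.

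- The power does not match the effect size it is said to rest on. An eta-squared of 0.425 is very large, and with 120 participants it should give power close to 1.
- The effect size is of the wrong kind. It compares healthy men with healthy women. An interaction asks whether that difference is larger or smaller in patients, and a sample with no patients cannot answer that. The Rationale in the appendix adds that the cited sex difference came only from the sagittal plane and from a set-up needing active trunk co-contraction, while this study measures passive stiffness in three planes.
- The powered test is not the hypothesised one. H1.1 is a sex difference within patients, and H1.2 is a group difference.

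This is the only power statement for Aim 1, and it accompanies the recruitment of 60 additional people. A reader who takes 0.85 at face value would treat a non-significant interaction as fairly strong evidence against one. The design supports that only for very large interactions.

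**Working it through.** **Inputs from the appendix.** Eta-squared 0.425; N = 120 (60 patients, 60 controls); 33 women and 27 men among the patients, hence also among the sex-matched controls; alpha 0.05, taken as two-sided. No dropout is stated for Aim 1, so none is applied.

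**1. Attempt to reproduce 0.85.** For a 1-df effect in a 2 x 2 design, f² = η²/(1 − η²), the noncentrality is λ = N·f², and the error df are 120 − 4 = 116.

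- f² = 0.425/0.575 = 0.739, so λ = 120 × 0.739 = 88.7.
- Power is above 0.9999.

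Other readings do not recover 0.85. With 60 participants, with alpha divided by six, or with a MANOVA of six responses, power stays above 0.9999. Reading 0.425 as Cohen's f gives 0.996, as a correlation 0.999, and as a standardised difference d 0.64.

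**2. What 0.85 would require.** Solving for power 0.85 with df 1 and 116 gives λ = 9.13. Then f² = 9.13/120 = 0.076 and η² = 0.076/1.076 = 0.071, about one sixth of the cited value.

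**3. The interaction on the SD scale.** The contrast is (men − women in patients) − (men − women in controls). In units of the within-cell SD its standard error is √(1/33 + 1/27 + 1/33 + 1/27) = √(2/33 + 2/27) = 0.367. The sizes below are assumptions.

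| Difference between the two sex differences | Power |
|---|---|
| 0.50 SD | 27% |
| 0.75 SD | 53% |
| 1.00 SD | 77% |
| 1.11 SD | 85% |

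**4. Can the cited effect be linked to the interaction?** With equal groups, d = 2f = 2 × √0.739 = 1.72 between the sexes. Interaction power then depends on how much back pain is assumed to change that difference, which the plan does not say.

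| Assumed change in patients | Interaction | Power |
|---|---|---|
| 25% | 0.43 SD | 21% |
| 50% | 0.86 SD | 64% |
| 75% | 1.29 SD | 94% |
| 100% | 1.72 SD | 99.6% |

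**5. The two hypotheses actually stated** (two-sample t test, two-sided 0.05; d values assumed).

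| Contrast | d = 0.4 | d = 0.5 | d = 0.8 | d for 85% power |
|---|---|---|---|---|
| H1.1, 33 v 27 patients | 33% | 47% | 86% | 0.79 |
| H1.2, 60 v 60, unpaired | 58% | 78% | 99% | 0.55 |

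The 86% for H1.1 at d = 0.8 is close to 0.85 by coincidence: it uses neither the cited effect, nor 120 participants, nor the interaction.

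**The case against.** The plan says its power is based on the cited data, not that 0.425 was entered as the interaction effect. If the implied sex difference of 1.72 SD changed by about 64 to 65% in patients, the interaction would be about 1.11 SD and the power about 0.85. The healthy-sex difference is one of the two differences in the contrast, so it is not irrelevant. The general objective, to study effects of sex in patients compared with matched controls, can be read as an interaction, and the 2 x 2 model contains one. If d = 1.72 carried over to patients, H1.1 would have power above 0.999, and half that effect (0.86) would give 90%. Matching could also help H1.2: with an assumed within-pair correlation of 0.2 to 0.5 and a paired analysis, power is 67 to 86% at d = 0.4 and 85 to 97% at d = 0.5. Finally, 60 controls follows largely from one-to-one matching to a patient group already sized on another outcome.

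Much of this stands as qualification. Aim 1 is not shown to be underpowered, some restated figures may be more favourable than 0.85, and the unpaired H1.2 figures are conservative if matching is used and effective. The plan attaches 0.85 only to the interaction, so it makes no claim about a null H1.2. None of this supplies the missing step. The 64 to 65% change is obtained by working backwards from 0.85 and appears nowhere in the documents. Even if the objective is read as an interaction, the hypotheses listed for Aim 1 do not include one.

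**Conclusion.** The concern holds: the power sentence is wrong as written. Taken directly, the cited effect gives power above 0.999; 0.85 needs an eta-squared of about 0.071, equivalent to an interaction of about 1.11 SD, which the plan neither states nor justifies. The powered test is neither of the two Aim 1 hypotheses, for which no power is given. These results assume a two-sided 0.05 test, complete data, cells of 33/27/33/27 and a single stiffness response. The power figures at particular effect sizes rest on assumed values. The consequence is confined to Aim 1 of the supplement; no randomised comparison in the parent trial is affected.

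**What to change.** Under Number of Subjects and Power, replace the interaction sentence with statements for the two Aim 1 hypotheses. For example, at two-sided 0.05 the design has 85% power for a difference of 0.79 SD between male and female patients (H1.1), and 0.55 SD between patients and controls in an unpaired comparison (H1.2). State whether the matching will be used in the analysis and, if so, the assumed within-pair correlation.

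If the interaction is of interest, add it as a named hypothesis and say that 120 participants can detect a difference between the two sex differences of about 1.0 to 1.1 SD (77% power at 1.0, 85% at 1.11). The eta-squared of 0.425 may be kept as background for a sex difference in healthy people, but not as the basis for interaction power.

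The cost is one rewritten sentence or short paragraph. Sample size, recruitment and the analysis model need not change. The price is giving up a single reassuring figure: for a moderate interaction the honest power is well below 0.85.

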- Randomization & Stratification: The study statistician will use the R statistical language to block-randomize treatments stratified by sex for each of the three separate experiments. Specifically, within each experiment there will be two strata within which we will create blocks of 3 patients, where treatments are permuted. Based on the randomization table the study coordinator will assign subjects to the treatment arms. In instances where multiple experiments are actively enrolling study participants and a participant meets eligibility requirements for more than one experiment, we will then use an adaptive randomization method to allocate them to one of the experiments. This method ensures that an experiment with fewer participants enrolled will have a higher allocation ratio. Specifically, with two potential experiments, the allocation ratio for Experiment  $i$  ( $p_i$ ) will be  $p_i = 1 - n_i/N$ , where  $n_i$  is the sample size for Experiment  $i$  and  $N$  is the total sample size thus far enrolled. With three active experiments, the allocation ratio will be  $p_i = (1 - n_i/N)/2$ . Note that this allocation to an experimental measurement group occurs prior to the randomization to a treatment arm.
- Masking or Blinding: In the RELIEF Study the principal investigators, the statistician, and members of the data collection team will remain blinded to intervention assignment throughout the duration of the study. They will be given the identifying codes only at the end of the study when it is necessary to interpret the results of the study. The un-blinded study coordinator, who is responsible for scheduling testing and treatment sessions, will serve to receive the study patients and escort them to the various testing and treatments sites to minimize the interaction between patients; however, the study coordinator will not participate in the assessments.

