### 9.1 General Design Issues

#### Mechanistic Component

Below we list our primary and secondary hypotheses for the Mechanistic Component. Note that all sample size calculations are based on the primary hypotheses. For more specific information, see *Data Analysis* below.

- Group 1 (Muscular Effects):
  - Primary Hypothesis
    - We hypothesize that there is a significant effect of treatment on skeletal muscle proton transverse relaxation time (T2) asymmetry of the lumbar muscles either immediately following the first treatment intervention (OA2), post-treatment measure (OA3), and/or follow-up measure (OA4), after controlling for the baseline outcome value.
- Group 2 (Spinal Effects)
  - Primary Hypothesis
    - For short-latency stretch reflex excitability, we hypothesize that there is a significant effect of treatment on this outcome at OA2, OA3, and/or OA4, after controlling for the baseline outcome value.
  - Secondary Hypotheses
    - For trunk muscle onset latencies in response to postural perturbations, we hypothesize that there is a significant effect of treatment on the principal component score (i.e., the linear combination of onset latencies of eight muscles) at OA2, OA3, and/or OA4, after controlling for the baseline outcome value.
    - For lumbar motion during volitional movement tasks, we hypothesize that there is a significant effect of treatment on the principal component score at OA2, OA3, and/or OA4, after controlling for the baseline outcome value.
  - See appendix for hypotheses of the supplemental research
- Group 3 (Cortical Effects)
  - Primary Hypothesis
    - We hypothesize that there is a significant effect of treatment on measures indicative of increased intracortical excitability (i.e., increased motor evoked potential amplitude, increased intracortical facilitation, and/or decreased short-interval intracortical inhibition) at either OA2, OA3, and/or OA4, after controlling for the baseline outcome values.

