  - The primary dependent variable (DV) for this group is the short-latency stretch reflex amplitude. Our preliminary work indicates that spinal manipulation reduces stretch reflex amplitude in individuals with chronic LBP who exhibit an audible joint sound by 30% from 0.56 to 0.39.[61] In study participants with no audible joint sound, there was a non-significant 10% increase from 0.62 to 0.68. The baseline standard deviation was 0.25 for both groups. We assumed manipulation would result in a 25% reduction 2-days following a course of treatment and a 20% reduction 4-weeks post course of treatment. Given our pilot data indicating the importance of cavitation, we assumed smaller reductions in stretch reflex amplitudes at each time point for the joint mobilization treatment arm. (i.e., 28, 23, and 18% reductions at the three endpoints). Finally, we assumed that Sham Control would have the same mean (0.68) at each testing point.
  - Our simulation studies indicate that 20 participants in each of the 3 Groups were sufficient to achieve power of 0.80 to detect a significant Group effect either immediately following treatment #1, 2-days following a course of treatment, or 4-weeks post course of treatment given an attrition rate of 10% and appropriate alpha adjustments.
  - See appendix for sample size and randomization regarding supplemental research
- Group 3 (Cortical Effects):
  - Changes in cortical excitability following manual therapy treatments are assumed to follow our observed changes in spinal reflex excitability. Accordingly, we assume the same magnitudes of changes for these DV's as detailed above. Specifically, we assume a 30%, 25%, and 20% reduction in measures of intracortical excitability in the manipulation treatment arm immediately following treatment #1, 2-days following a course of treatment, and 4-weeks post course of treatment, respectively. Likewise, we assumed 28%, 23%, and 18% reduction for the mobilization treatment arm, and no change for the sham treatment arm. The residual variance was set at 50% of the initial value, similar to the Group 2 variables.
  - Our simulation studies indicate that 20 participants in each of the 3 Groups were sufficient to achieve power of 0.80 to detect a significant Group effect either immediately following treatment #1, 2-days following a course of treatment, or 4-weeks post course of treatment given an attrition rate of 10% and appropriate alpha adjustments.

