### **Detailed Analytic Approach:**

Linear mixed-effects regression (LMER) analyses will serve as the main analytic framework, because it offers distinct advantages in statistical power and estimation of population parameters over ANOVA or MANOVA. First, LMER easily incorporates miscellaneous factors (e.g., blocks and treatment providers) as random effects so that the variances due to those factors can be partitioned. As a result, LMER models typically offer less biased parameter estimation and can also offer higher statistical power. It can model multiple dependent variables (e.g., motor evoked potential amplitude, intracortical facilitation, and short-interval intracortical inhibition for Group 3) and test the effect of treatment for each of these dependent variables simultaneously. This modeling technique avoids alpha inflations which typically result from multiple testing. Finally, LMER's maximum-likelihood estimation allows patients with missing observations to be included in a model if the observations are missing completely at random or missing at random. This advantage is important because some degree of attrition is unavoidable given the longitudinal nature of our project. Because we will stratify our samples by sex, sex will be included in each of the models we will describe below. We will test the significant main effect of sex as well as its interaction with the Treatment factor.

- **Intention to Treat Analysis (ITT):** We will include all randomized study participants who have at least baseline endpoint assessments in our ITT analysis. The ITT analysis is our primary method for assessing outcomes, and how it is performed will be determined based on the pattern of

missingness. If the missingness is deemed MCAR, the LOCF method will be used: simply the most recent valid observation will be "carried forward" to replace the subsequent missing observations. If the missingness is deemed MAR, missing observations will remain as missing, and maximum-likelihood estimation, the default estimation algorithm of LMER, will be used to estimate these observations. If the missingness is found to be MNAR, multiple-imputed data will be used to construct LMER models.

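### The power claim for the Aim 2 sex question (supplement appendix) is not supported by sections 9.1–9.2, and H2.1 is a null hypothesis with no criterion that could establish it

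*Supplement*

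**What the plan says.** The appendix, under Number of Subjects and Power, gives no numerical power for Aim 2. It borrows from the parent trial, whose initial estimates are described as "designed to detect gender differences as well as treatment effects on trunk onset muscle latencies, and assuming similar effect sizes for our trunk stiffness measures". It concludes that "60 participants with chronic LBP should provide sufficient power for the stiffness measures in aim 2 of this application". It also fixes the sex split: "our sample for Experiment 2 will consist of 33 females and 27 males".

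Under Hypothesis Testing: Aim 2, H2.1 reads "There are no net sex effects of spinal manipulation on trunk stiffness". The planned test is a mixed-model MANOVA with three treatment groups, two sexes and three times (baseline, after the first treatment, and 48 hours after the course). No margin, interval rule or interaction power accompanies it.

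Section 9.1 of the main protocol says of the mechanistic component: "Note that all sample size calculations are based on the primary hypotheses". It lists trunk muscle onset latencies as a secondary hypothesis of Group 2. Section 9.2 says of Group 2: "The primary dependent variable (DV) for this group is the short-latency stretch reflex amplitude". It claims 0.80 power with 20 per arm for a group effect.

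Sex enters the parent plan in two other places. Section 3 will "block-randomize treatments stratified by sex for each of the three separate experiments", and section 9.5 says "We will test the significant main effect of sex as well as its interaction with the Treatment factor".

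**The concern.** The statement that carries Aim 2 does not match the calculation it refers to. Section 9.2 contains neither a sex effect nor a calculation for onset latencies, and the appendix's own first paragraph on power repeats the reflex-amplitude basis.

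This matters more than usual because H2.1 is the statement of no difference. A test of a point null can reject it but cannot establish it, and the smaller the power, the more often the test fails to reject. The sex question in treatment response is one of the supplement's two stated objectives. A null result from this analysis would say little about whether the treatments act differently in men and women, yet the appendix tells the reader that the sample is adequate.

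**Working it through.** **1. The passages side by side.**
- Outcome: the appendix says onset latencies; section 9.2 uses stretch reflex amplitude, and section 9.1 ranks onset latencies as secondary.
- Effect: the appendix says gender differences and treatment effects; section 9.2 powers a three-arm group effect.
- Inputs in section 9.2: alpha 0.05, AR(1) with rho −0.50, Holm adjustment, 10% attrition, baseline covariate, reductions of 30/25/20% (manipulation) and 28/23/18% (mobilization), sham flat at 0.68, SD 0.25. None is a sex or sex-by-treatment term.

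**2. The parent figure, 0.80 for the group effect.**
Take n = 18 per arm (20 less 10%), difference 0.30 × 0.68 = 0.204, and residual SD 0.25 × √(1 − 0.5²) = 0.2165.
- SE = 0.2165 × √(2/18) = 0.0722, and 0.204/0.0722 = 2.83.
- Power = Φ(2.83 − 1.96) = 0.81.

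Simulation of the three-arm test with Holm, a common baseline of 0.62 and rho −0.5 gives 0.79. Other readings of the unstated arm baselines give 0.59 to 1.00. So 0.80 is reachable, but only for the group effect.

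**3. The sex-by-treatment contrast, closed form.**
Cells: 33/3 = 11 women and 27/3 = 9 men per arm. For manipulation versus sham, women versus men, in outcome SD units:
- SE = √(2/11 + 2/9) = 0.636, multiplied by √(1 − r²) when baseline is adjusted with correlation r.
- Test: two-sided 0.05, noncentral t, 53 df.

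The documents give no stiffness effect or SD. The appendix assumes similar effect sizes to the parent trial, so the reflex figures stand in. They can be read in three ways, for an effect present in one sex only:

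| Reading | Effect | r = 0 | r = 0.5 | r = 0.7 |
|---|---|---|---|---|
| 0.56 to 0.39 | 0.17/0.25 = 0.68 SD | 0.18 | 0.23 | 0.31 |
| 30% of 0.68 | 0.204/0.25 = 0.82 SD | 0.24 | 0.31 | 0.42 |
| 0.39 against sham 0.68 | 0.29/0.25 = 1.16 SD | 0.43 | 0.54 | 0.71 |

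The values of r are assumptions. The interaction detectable with 80% power is 1.81, 1.57 and 1.30 SD for r = 0, 0.5 and 0.7. Without baseline adjustment, the 95% CI half-width is about 1.96 × 0.636 = 1.25 SD. These figures allow for no dropout. With 10% attrition the 0.82 SD row becomes 0.22 to 0.39.

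**4. The planned MANOVA, by simulation.**
The group-by-sex-by-time term was tested on baseline, the first post-treatment measure and the post-course measure, with 11 women and 9 men per arm and the planned reductions in one sex only.
- Common baseline 0.68: power 0.10–0.16 for rho from −0.5 to 0.5, and about 0.35 at rho 0.8.
- Common baseline 0.56: 0.08–0.13, and 0.22–0.26 at rho 0.8.

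Every rho except −0.50 is an assumption.

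**5. Size needed.**
For 80% power at the post-course effect (0.25 × 0.68 = 0.17), the number per sex-by-arm cell is 4 × SD² × (1.96 + 0.84)² / 0.17².
- SD 0.2165: 51 per cell, 6 × 51 = 306 in all.
- SD 0.25: 68 per cell, 6 × 68 = 408 in all.

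The plan has 60.

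**The case against.** **Whether a calculation existed.** A reader might infer that a gender-powered calculation was never made. The documents do not show that. The appendix refers to the parent grant's initial estimates, and the grant application is not among the documents. What they show is that this protocol reports no such calculation, and that one would sit badly with section 9.1's statement about all sample sizes. The mismatch stands either way.

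**How a null result would be used.** A reader might also infer that a non-significant MANOVA will be reported as confirming H2.1. No passage says so. Aim 2 is worded as examining sex differences, and the appendix elsewhere says only that the influence of sex will be assessed. What stands is narrower: the plan states a null hypothesis and gives no criterion by which it could be supported.

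**The size of the shortfall.** Any single miss rate would be too precise. The closed-form contrast is not the planned test, the choice among 0.68, 0.82 and 1.16 SD is open, and the correlations are assumed. Favourable readings do pass 0.5:
- 1.16 SD gives 0.54–0.71 with r of 0.5 to 0.7.
- Both manual arms pooled against sham, at 0.82 SD and r = 0.7, give 0.53.
- The contrast right after the first treatment gives about 0.55 at rho 0.8. It gives about 0.74 if the effect in the responding sex is nearly doubled, so that the average matches the plan. The planned MANOVA then still has only 0.27–0.45 (baseline 0.68).

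**Section 9.5.** It is tempting to extend the point to the sex-by-treatment tests there. They follow from stratification, no power claim attaches to them, and section 9.1 lists no sex hypothesis for the parent trial. No change is needed.

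**Weight.** This is an ancillary aim, and 18 + 31 = 49 of the 60 Experiment 2 patients had already been tested. Aim 1 has its own power statement. No parent endpoint, sample size or safety rule is affected.

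**Conclusion.** The concern holds in this form. The appendix attributes to the parent trial a power basis that sections 9.1–9.2 do not support. H2.1 is a null hypothesis that the planned MANOVA cannot establish without a margin or an interval criterion. Power for an effect confined to one sex is low under most readings: about 0.18–0.42 for the single contrast at 0.68–0.82 SD with baseline correlation 0 to 0.7, and about 0.10–0.35 for the planned MANOVA (somewhat lower with the 0.56 baseline). These figures use reflex inputs in place of stiffness inputs, equal allocation within sex, and assumed correlations. The direction is secure under most readings, but the exact value is not. The point should be fixed, but it does not threaten the parent trial's conclusions.

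**What to change.** In the appendix, Number of Subjects and Power:
- Delete or correct the sentence saying that the parent trial was powered for gender differences and onset latencies.
- For the Aim 2 sex question, replace the claim of adequate power with a statement that the sex-by-treatment analysis is exploratory.
- Give the detectable interaction with its assumptions beside it: contrast, SD, baseline correlation and attrition. On the closed form above it is 1.3–1.8 SD for r from 0.7 to 0, before attrition.

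In Hypothesis Testing: Aim 2:
- For H2.1, report the sex-by-treatment difference in stiffness change with its 95% CI, or pre-specify an equivalence margin.
- State that non-significance will not be reported as absence of a sex effect.

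The cost is wording and a less favourable power statement. It needs no extra patients, data or procedures.
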